**Endovascular treatment technique and intraoperative response to thrombus.**

　Cerebral aneurysm embolization with EVT within 72 h of presentation. EVT is performed under general anesthesia. Administration of a specified number of drugs (aspirin 200 mg or lactose 200 mg) at the time of enrollment/allocation will be performed by the physician in charge of anesthesia or the study sub-investigator via the gastric tube after induction of general anesthesia. The surgeon group will not be administered any visible medication. A cerebral aneurysm embolization will be performed.

Cerebral aneurysm embolization is performed via the transfemoral, radial, brachial, and carotid arteries and a guiding catheter is placed in the internal or vertebral carotid artery. Intraoperatively, heparin, an anticoagulant, is administered intravenously at the discretion of the surgeon, and systemic heparinization is performed to activate coagulation time (ACT) from 250 s to 300 s. A microcatheter and microguidewire are used to place the microcatheter in the aneurysm. A coil for aneurysm embolization is placed in the aneurysm via a microcatheter placed in the aneurysm. If needed, a distal access catheter that allows stable distal vascular access, balloon catheter neck modeling, and double-catheter embolization with two microcatheters may be used. Treatment is terminated when sufficient embolization is achieved to prevent aneurysm re-rupture.

Intraoperatively, if there is evidence of cerebral angiographically evident thrombosis around the aneurysmal neck or in the parent artery (primary endpoint 1), ACT will be measured again immediately, and heparinization will be intensified to provide an ACT > 300 s, or Ozagrel Sodium 80 mg administered intravenously. To confirm the resolution of the thrombus, repeat angiography will be performed as appropriate. If there is a tendency to exacerbate the thrombus, endovascular procedures such as thrombus disruption with a balloon catheter and thrombus retrieval with a stent retriever or thrombus aspiration catheter should be considered. When required, the emergency key of the case will be opened to check the details of the drug administered promptly; if the drug administered is aspirin powder 200 mg, clopidogrel 300 mg will be administered, or if the drug administered is lactose 200 mg, aspirin powder 200 mg and clopidogrel 300 mg will be administered via a nasogastric tube.

　If stent placement is judged to be required due to significant deviation of the coils into the parent artery during the operation, the emergency room should be opened and the medication checked. Clopidogrel 300 mg (or aspirin 200 mg and clopidogrel 300 mg) should be administered via a nasogastric tube to load the antiplatelet agent, and intracranial stent placement should be performed.

**Standard postoperative management**

MRI will be performed within 6–48 h after surgery, and assessment of ischemic lesions and concordant neurological dysfunction will be performed by the investigator and sub-investigator (INV), as well as assessment by IRC separately, with the outcome of IRC as the primary endpoint (primary endpoint 2). Assessment by IRC is based on CT simplex or MRI (CTA or MRA of the head before surgery, plain CT of the head within 48 h after surgery, clinical information on the cerebral aneurysm at the time of surgery (prior treatment of the aneurysm, location, surgical intervention before the treatment of the aneurysm), and worsening of surgical intervention and neurological outcome after the treatment of the cerebral aneurysm between the time of surgery and MRI imaging.

Postoperatively, the patient is managed systemically with standard-of-care (continuous intravenous infusion of nicardipine hydrochloride 120-600μg/kg/Hr, intravenous fasudil hydrochloride hydrate 90 mg/day, ozagrel sodium 80 mg/day, etc.) for cerebral vasospasm discussed at the participating institutions. However, the dose may change at the discretion of each institution. If perioperative surgical intervention, including cerebrospinal fluid drainage or EVT for symptomatic cerebral vasospasm (percutaneous cerebral angioplasty or fasudil hydrochloride hydrate arterial infusion therapy), is required, it should be performed at the discretion of the individual institution. The basic protocol requires a head CT performed within 48 h after surgery and 14 ± 2 days after surgery. Imaging will be performed as appropriate during this period, and all cerebral ischemic events within 14 days after MRI and all hemorrhagic events within 14 days after enrollment will be evaluated. In addition, the mRS score 3 months after the onset of subarachnoid hemorrhage will be assessed by the investigator and sub-investigator in the outpatient clinic on a face-to-face basis. If the patient cannot visit the hospital or is hospitalized in another hospital, the patient will be evaluated via telephone interviews.

## **6-1.** **Type and design of studies**

　This will be a randomized, placebo-controlled, double-blind, parallel-group study.

## **6-2.** **Study period**

Period of study: 4.25 years (jRC announcement date: March 31, 2026)

　 Case registration period: 3 years (January 1, 2022 - December 31, 2024)

　 Inclusion, implementation, and observation period: 3.25 years (January 1, 2022 - March 31, 2025)

## **6-3.** **Dosage and administration and duration of administration of the research drug**

After obtaining and assigning informed consent, when performing aneurysm embolization for a ruptured cerebral aneurysm, a nasogastric tube is inserted after induction of general anesthesia, and aspirin-powder 200mg or placebo-lactose 200mg is dissolved in tepid-water 20mL via a nasogastric tube.

・Aspirin (Aspirin)

Date of approval: August 6, 1985

　Approval Number: 16000AMZ03805000

　Manufactured and marketed by Mylan Pharmaceutical Co., Ltd.

　Sales: Pfizer Pharmaceuticals Inc.

　Dosage form: powder (crystals)

　Storage: Storage at room temperature

・Lactose (Lactose Hydrate)

Manufacturing approval Date: February 1, 2008

Approval Number: 27A2X00206

Manufactured and marketed by Mylan Pharmaceutical Co., Ltd.

　Sales: Pfizer Pharmaceuticals Inc.

Dosage form: powder (crystals)

　Storage: Storage at room temperature

## **6-4.** **Patient registration and allocation method**

<Methods of case registration>

The investigator or sub-investigator,

1. Written consent shall be obtained from the patient or proxy consenter.
2. Interactive Web Response Systems(IWRS) enter the inclusion/exclusion criteria, and allocation adjustment factors, and receive the drug number.
3. Receive the study drugs (two packages including the reserve) for the drug number. Test drugs are anesthetic

Hand it to your doctor. Properly manage the unused reserve after surgery and at a later date.

dispose of the drug at each facility when it expires.

<Methods of Randomization>

Each center will be allocated 1:1 to aspirin-and placebo-treated groups by dynamic allocation (minimization method) with age (≧65 years, <65 years), sex (male, female), World Federation of Neurosurgical Societies (WFNS) grade (I-III, IV-V), and modified Fisher grade (0-2, 3-4 as allocation-adjusted factors.

<How to blind study drugs>

In this study, a double-blind method will be employed, and the study personnel and participants, other than the pharmacist preparing the study drug and allocation manager will be blinded.

1. Confirm the indistinguishability of the test drug.
2. A corresponding table will be prepared consisting of the allocation group (aspirin or placebo) and the drug number.
3. The drug number is assigned to the test drug based on the corresponding table.
4. Provide the correspondence table to the allocation system administrator.
5. The corresponding table should be stored until unblinding and should not be disclosed to other persons. Unblinding is not to be performed until the test is completed, and the collection or exclusion of each participant is fixed, except during an emergency.

To ensure the quality of the test drug, the procedure for preparation of the test drug and blinding is carried out approximately every 3 months.

<Opening the emergency key>

When the principal investigator or sub-investigator judges that the occurrence of a serious adverse event for which a causal relationship to the investigational drug cannot be ruled out or the appearance of thrombus formation evident on cerebral angiography around the aneurysm or in the parent artery during surgery requires the opening of an emergency key to ensure the safety of the participant, the emergency key will be opened in the allocation system to check the allocation of the investigational drug in the relevant participant and take appropriate action. If an emergency key is opened, the principal investigator or sub-investigator records the reason for disclosure and immediately contacts the test office.

## 6-5. Responses after study completion

Continue treatment in routine insurance practice after completion of the study

# **7.** **Endpoint**

## **7-1.** **Items related to the evaluation of efficacy**

　Primary outcomes

1) Incidence rate of intraoperative thrombotic complications

It is defined as the proportion of patients with evidence of cerebral angiographically evident thrombus formation in the vicinity of the aneurysm neck or parent artery during surgery.

2) Incidence rate of symptomatic ischemic lesions on MRI diffusion-weighted imaging (DWI) evaluated by the Independent Review Committee (IRC)

It is defined as the percentage of patients with acute-phase ischemic lesions on MRI-DWI performed 6–48 h postoperatively and with concordant neurologic findings.

Key secondary outcomes

1) Incidence rate of all bleeding events within 14 days of enrollment

As a basic protocol, a head CT is performed within 48 h postoperatively and at 14±2 days postoperatively. Additionally, imaging evaluations were conducted as required. The incidence rate of all bleeding events is defined as the percentage of patients with a ruptured aneurysm (symptomatic subarachnoid or intracerebral hemorrhage due to rupture of an aneurysm of interest), a hemorrhagic stroke (symptomatic subarachnoid and intracerebral hemorrhage not due to rupture of target aneurysm, or the proportion of patients who experienced "major hemorrhage" according to ISTH criteria within 14 days post-registration.

2) Incidence rate of cerebral ischemic events in the first 14 days after MRI

The basic protocol is head CT performed within 6–48 h after surgery and 14 ± 2 days after surgery. This is defined as the percentage of patients with transient ischemic attack within 14 ± 2 days after MRI (neurological symptoms lasting less than 24 h with or without imaging findings) or ischemic stroke (focal neurological symptoms lasting more than 24 h and ischemic lesions confirmed by head CT or MRI) during the study period.

Other secondary outcomes

1) Incidence rate of symptomatic ischemic lesions in MRI-DWI evaluated by INV.

2) mRS at 3 months

Assessment is based on mRS scoring 3 months after the onset of subarachnoid hemorrhage.

　Exploratory outcomes

1) Ischemic lesions on MRI-DWI (number and size: 0–4 mm, 5–9 mm, 10–14 mm, 15 mm or greater, categorized as IRC or INV)

2) Incidence rate of cerebral hemorrhage along the tube tract for ventricular drainage on CT scans in the first 14 days after EVT.

## **7-2.** **Items related to safety evaluation**

**Evaluation of adverse events and diseases**

**Definition of adverse events**

An adverse event (AE) is any untoward medical occurrence in a participant receiving treatment and does not necessarily indicate a causal relationship with the study treatment. An adverse event can, therefore, be any unfavorable or unintended sign (including an abnormal laboratory finding), symptom, or disease occurring at the time of treatment, regardless of whether it is considered treatment-related. The case report form should include the name of the adverse event, date of onset, outcome, and causal relationship with the antiplatelet agents.

A serious adverse event (SAE) was defined as any of the following:

1) Death;
2) Life-threatening;
3) Those requiring hospitalization for treatment or prolongation of hospitalization;
4) Permanent or significant disability/dysfunction;
5) Congenital anomalies in offspring

**Definition of disease**

Adverse events suspected to be caused by the conduct of this study (diseases, disability, death, and infectious diseases, including abnormal laboratory values and symptoms) are referred to as diseases. A causal relationship with the study drug or procedure cannot be ruled out. Causality was determined by the investigator or sub-investigator.

Additionally, for diseases corresponding to serious adverse events, the procedures in 10-2 should be followed.

**Causality assessment**

The principal investigator or sub-investigator will determine whether there is a causal relationship between adverse events (death, occurrence of major hemorrhagic events, re-treatment of the target cerebral aneurysm, and re-bleeding of the target cerebral aneurysm) that occurred during this study and the causal relationship of this study.

1) Causality/causality cannot be ruled out: temporally related to study drug administration or procedures, reasonably judged to be due to the study drug or procedure, or unrelated to the study drug.

2) No causality: It can be judged as not being related based on the temporal relationship with the administration of the test drug or test procedure.

**Adverse event reporting**

Adverse events (death, occurrence of major hemorrhagic events, retreatment of the target cerebral aneurysm, and rebleeding of the target cerebral aneurysm) will be recorded in a case report form. Diseases, among other SAEs, are reported based on the procedures in 10-2.

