# **10. Handling of adverse events**

## **10-1. Response to patients when adverse events occur**

When adverse events are observed, the principal investigator or sub-investigator should promptly take appropriate measures and describe them in the medical records and eCRF without any discrepancy.

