**Analysis of safety endpoints**

1) Adverse event rates

2) Incidence of adverse reactions

The numbers and percentages of patients in each group are calculated for SAS.

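### The protocol contradicts itself on which adverse events are recorded and rated for causality, so the content of both safety endpoints is unsettled, mainly for non-serious events

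*Protocol*

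**What the plan says.** Section 7-2 opens broadly: "An adverse event (AE) is any untoward medical occurrence in a participant receiving treatment". It adds that the case report form should hold each event's name, onset date, outcome and causal relationship. Its Definition of disease covers events suspected to be caused by the study, including abnormal laboratory values and symptoms, and leaves causality to the investigator.

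Two later paragraphs of 7-2 are narrower. Causality assessment attaches a list of four event types (death, major bleeding, retreatment of the target aneurysm, rebleeding from it) to the causality judgment. Adverse event reporting attaches the same list to recording: "Adverse events (death, occurrence of major hemorrhagic events, retreatment of the target cerebral aneurysm, and rebleeding of the target cerebral aneurysm) will be recorded".

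Section 10-1 has no such list. The investigator is to act on observed adverse events and "describe them in the medical records and eCRF without any discrepancy".

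In section 14-3 the safety endpoints are "1) Adverse event rates" and "2) Incidence of adverse reactions", with this analysis: "The numbers and percentages of patients in each group are calculated for SAS".

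The first causality class in 7-2 is headed as covering events with causality, or with causality not ruled out. Its text includes events "reasonably judged to be due to the study drug or procedure, or unrelated to the study drug". The second class is for events with no causality.

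**The concern.** A safety rate is only as well defined as the rule for what enters its numerator. Here two paragraphs name a closed list of four types, with nothing to mark it as a set of examples, while the endpoints and several other sections have no list. Someone filling in the form can follow one instruction and breach another.

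The second endpoint depends on causality as well as on recording. An adverse reaction has to be an adverse event judged possibly related, so a restricted causality scope and overlapping classes both change its count.

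This cannot be left to the statistical analysis plan. Such a plan can choose among recorded events, but it cannot recover events that were never entered or causality that was never rated. The protocol states safety as part of the study's aim (section 1) and describes the aspirin use as off-label (section 16-3), so the two rates should be interpretable.

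**Working it through.** No arithmetic applies, because the point rests on no rate, margin or sample size. The check is a comparison of the text.

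**Step 1. Scope by place in the protocol**

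| Place | What it governs | Events covered |
|---|---|---|
| 7-2, Definition of adverse events | Definition; CRF content (name, onset, outcome, causality) | Any type |
| 7-2, Definition of disease | Causally suspected events | Any type, including laboratory findings |
| 7-2, Causality assessment | Causality rating | Four types |
| 7-2, Adverse event reporting | CRF recording | Four types |
| 8, day-14 and 3-month safety items | Scheduled questions | Any serious adverse event; retreatment |
| 8, event form | Events as they occur | Stroke events, ISTH major bleeding, a field for other adverse events |
| 10-1 | eCRF entry | Any type |
| 10-2 | Reporting of causally suspected events | Any type, mild ones in the periodic report |
| 14-3, safety endpoints | Analysis | Any type |

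Two rows are restricted to the four types. The others are wider.

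**Step 2. Follow three kinds of event through the rules**

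- *One of the four types.* Recorded and rated for causality under every paragraph.
- *Serious, but not one of the four* (for example anaphylaxis that prolongs the hospital stay). Not on the 7-2 list, but the section 8 questions on serious adverse events lead to the event form. If causally suspected, it falls under 10-2.
- *Non-serious and not one of the four* (for example a rash or a modest rise in liver enzymes). The definition in 7-2, section 10-1 and the field for other adverse events bring it in. Adverse event reporting in 7-2 does not. The scheduled day-14 and 3-month safety questions do not ask about it. Its causality is the investigator's to judge under the Definition of disease, but it is off the list in Causality assessment.

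The contradiction therefore bites mainly on the third kind.

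**Step 3. Count against the expected reactions**

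Section 7-2 lists seven groups of significant aspirin reactions. Five (anaphylaxis, severe skin reactions, blood disorders, asthma, hepatic disorder) match none of the four types unless fatal. The other two (hemorrhage, gastrointestinal ulcers) match essentially only through major bleeding, rebleeding or death. This count measures the gap between the list and the expected reactions. It does not measure lost data, because serious cases have the second route in Step 2.

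**Step 4. Compare the form with the requirement**

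The definition paragraph in 7-2 wants outcome and causality for each adverse event. The event form in section 8 has a date and details, but shows no causality item and no event-outcome item. The treatment-outcome entry on that form grades aneurysm occlusion after retreatment.

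**Step 5. Test whether the causality classes are exclusive**

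Take an event judged unrelated. It fits the second class by definition and the first class by its last clause. Read literally, the first class could hold every rated event, and the incidence of adverse reactions could rise to the full rate among rated events. The Definition of disease in 7-2 and section 10-2 point to the narrower meaning: a relationship that cannot be ruled out.

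**The case against.** Read as a whole, the protocol is broader than the two restricted paragraphs. A reader might infer that recording and causality rating are confined to four types throughout. The documents do not support that: 7-2 itself, section 8, 10-1 and 10-2 all go further. Nor do they show that most expected reactions would be missed, since serious ones reach the event form and causally suspected ones fall under 10-2.

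A reader might also infer that sites will split into two recording practices. One item list and one event form are specified for all, so this is possible but not shown. The trial is double-blind with 1:1 allocation at each center, so uneven recording is unlikely to favor an arm, apart from patients whose emergency key is opened. That limits bias in the comparison, but it does not make the percentages in each group interpretable.

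The clause about unrelated events looks like a drafting or translation slip. It need not push unrelated events into regulatory reporting, because 10-2 states its own criterion. It still has to be corrected, since it sits in the rule that defines the classes.

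Finally, the stakes are bounded. Section 14-3 calls only for counts and percentages, with no test, and bleeding, the main safety question, has its own definition as a key secondary outcome. All of this stands, and it narrows the point. It does not remove the conflict between stated rules.

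**Conclusion.** The point holds as an internal contradiction. The protocol gives two scopes for recording and causality rating, and the safety endpoints do not match the narrower one. Until the sections are reconciled, the content of both endpoints is unsettled, mainly for non-serious events outside the four types. It would go too far to say that neither rate has meaning: listed events are covered under every reading, and serious unlisted ones are captured.

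The two causality classes overlap as worded, which leaves the numerator of the adverse reaction incidence open.

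No numerical size can be given, because the protocol gives no expected adverse event frequencies for this trial. The conclusion assumes that the four-item list means what it says and that the form shown in section 8 is complete. The key secondary bleeding and ischemic outcomes have their own definitions and are not affected. The correction should be made, and it is nearly free.

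**What to change.** 1. State one adverse event scope and use it in 7-2, 10-1 and 14-3.
   - *Option A:* record and rate all adverse events. Remove the four-item restriction from the causality and reporting paragraphs of 7-2, and add the causality and outcome items that 7-2 requires to the event form in section 8. The cost is a form change and a small amount of extra data entry.
   - *Option B:* keep the four types, rename the 14-3 endpoints as rates of those listed events, and give up an overall adverse reaction incidence. Align the CRF sentence in 7-2 and section 10-1 with this. Reporting under 10-2 would still need a causality judgment on other events, so the text should say so. The cost is wording only.

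2. Reword the first causality class to cover events judged due to the study drug or procedure, or for which a relationship cannot be ruled out, and to exclude unrelated events. Deleting the stray clause alone is not enough, because the cannot-be-ruled-out half of the heading would then have no matching text. The two classes should be mutually exclusive and agree with the Definition of disease in 7-2 and with 10-2. The cost is one sentence.

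If patients have already been followed under the present text, Option A cannot restore events that were not entered. The safety tables should then state which scope was applied.
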